**Objectives**

To estimate the rate ratio for Parkinson’s disease in people with diabetes, comparing individuals treated with glitazones to people treated with agents other than glitazones.

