**Study Population**

The study population will be drawn from the entire CPRD population with acceptable up to standard (UTS) follow up time. People will be selected for inclusion if they have received any prescription for a GTZ antidiabetic (code list in Appendix 1), with the first occurrence being at least 12 months after the patient’s start of UTS follow up. This is to increase the likelihood that we are studying new users of GTZs, which will be of importance when we assess any effect of treatment duration on PD risk. Eligibility will begin in 1999 when the first GTZ was launched. No age restrictions will be applied to eligibility; the mean age of type 2 diabetes diagnosis in a US population was ~ 46 years in 2000 (Koopman et al, 2005) and so we anticipate the age profile of patients receiving GTZ antidiabetics will be a little younger than the typical onset age for PD (over 50 year), making them an ideal group in which to study the long term effects of a potentially neuroprotective agent. Potential participants with any diagnosis of PD prior to their first GTZ prescription will be excluded. Users will be classified according to their diabetes treatment stage at the time the GTZ is started, as follows:

1. GTZ monotherapy, no prior oral anti-diabetic (OAD)
2. GTZ monotherapy, previous OAD discontinued
3. Combined OAD therapy, GTZ being taken with other OADs

A feasibility count shows there are ~43,000 incident GTZ users with at least 12 months prior UTS follow up. Follow up for the study analysis will begin at the first prescription for a GTZ and end at the earliest of last collection date for the practice, patient transfer out or death date.

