**Selection of Comparison Group**

Each GTZ exposed patient will be matched by age, sex, and practice with up to 5 patients receiving other oral treatment for diabetes (unexposed group). To reduce the possibility of confounding, we will only select patients who have also received oral antidiabetic treatments, thus reducing the difference in disease stage between GTZ users and non-users. GTZ prescribing has evolved during >10 years according to changes in treatment guidance and changes made to the licensed indication. Initially they were mostly used as second line combination treatment, but were subsequently also used at earlier stages of diabetes treatment. Rosiglitazone was eventually suspended due to cardiovascular safety concerns and pioglitazone use has waned due to concerns over the risk of bladder cancer. To be considered for inclusion, only patients present in the database from 1999 onwards and with at least 12 months UTS follow up prior to prescribing events that trigger eligibility will be included. For instance a patient could be matched to a GTZ user in category 1) above if they had never received an OAD before 1999 and began taking a sulphonylurea with no other OAD after at least 12 months UTS follow up. Follow up for the unexposed will begin at the first prescribing event that makes them eligible for inclusion.

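### Treatment stage and comparator selection are defined by oral drugs only, so insulin use is neither balanced nor adjusted for

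*Protocol*

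**What the plan says.** Under Study Population, the GTZ arm is open to anyone ever prescribed the class: "People will be selected for inclusion if they have received any prescription for a GTZ antidiabetic". No condition is set on insulin use. The section then states a purpose: "Users will be classified according to their diabetes treatment stage at the time the GTZ is started". Three categories follow:

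1. "GTZ monotherapy, no prior oral anti-diabetic (OAD")
2. "GTZ monotherapy, previous OAD discontinued"
3. "Combined OAD therapy, GTZ being taken with other OADs"

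Under Selection of Comparison Group, matching is on age, sex and practice, with up to five comparators per GTZ user. Comparators are also chosen by oral treatment: "we will only select patients who have also received oral antidiabetic treatments, thus reducing the difference in disease stage between GTZ users and non-users". The worked example for category 1 is a person for whom "they had never received an OAD before 1999 and began taking a sulphonylurea with no other OAD" holds, after at least 12 months of up-to-standard follow-up.

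Under Exposures, Outcomes and Covariates, exposure is read from prescribing records with code lists for the individual oral drugs. The diabetes-related covariates are time since diagnosis, HbA1c at index, time-updated HbA1c and metformin. Insulin is not listed.

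**The concern.** The design relies on both arms having diabetes at a similar stage. The protocol gives this as its reason for restricting comparators, and it treats diabetes itself as possibly associated with PD. A stage definition that leaves out a whole class of glucose-lowering treatment cannot fully deliver that. Two GTZ starters with the same oral history, one on insulin and one not, receive the same stage and draw comparators under the same rule.

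If insulin use differs between the arms, and if insulin users have a different PD rate, the primary rate ratio carries part of that difference. Nothing in matching balances insulin, and no listed covariate measures it directly. The protocol considers a 25% reduction clinically meaningful, so a shift of a few percent would matter to the interpretation without being obvious in the results.

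**Working it through.** **The plan's own figure.** The only calculated figure in the protocol is the power. Take 144 PD events in 43,000 exposed patients (0.335%) as the exposed rate, that rate divided by the rate ratio as the unexposed rate, five comparators per exposed patient, and a two-sided 5% level (assumed, as none is stated). A two-proportion calculation then gives 99.0%, 92.0% and 71.8% for reductions of 30%, 25% and 20%, against the stated 99%, 91% and 71%. The figures reproduce. The present point does not depend on them.

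**Where an insulin user who starts a GTZ is placed.**

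| Oral history at GTZ start | If staged on oral drugs alone | If "monotherapy" is taken to exclude insulin |
|---|---|---|
| None | Category 1 | No category |
| Earlier oral drug stopped | Category 2 | No category |
| Another oral drug continuing | Category 3 | Category 3 (does not use the term) |

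The protocol does not say which column applies. In the left column the stage ignores insulin. In the right column some eligible patients have no stage, and so no comparator rule. The comparator side has the same gap: an insulin user starting a first sulphonylurea meets the category 1 example as it is worded.

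**Size.** Let fE and fC be the shares of insulin users among GTZ users and comparators, and k the PD rate of insulin users relative to the rest. If nothing else differs, the rate ratio is multiplied by

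(1 + fE(k-1)) / (1 + fC(k-1)).

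The protocol gives none of the three inputs. All values below are assumptions.

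| fE | fC | k | Factor | A true 0.75 would read |
|---|---|---|---|---|
| 20% | 20% | any | 1.00 | 0.75 |
| 20% | 10% | 1.2 | 1.04/1.02 = 1.020 | 0.76 |
| 20% | 10% | 1.5 | 1.10/1.05 = 1.048 | 0.79 |
| 20% | 0% | 1.5 | 1.10/1.00 = 1.10 | 0.825 |
| 10% | 20% | 1.5 | 1.05/1.10 = 0.955 | 0.72 |
| 20% | 0% | 0.8 | 0.96/1.00 = 0.96 | 0.72 |

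The factor can fall on either side of 1, and it vanishes when the shares are equal.

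**What the planned adjustment would catch.** Diabetes duration and HbA1c are candidate covariates. HbA1c reflects glucose control under whatever treatment is being given, so it does not identify insulin users, and duration does so only loosely. Under Statistical Analysis, a variable is retained only if it changes the rate ratio by 10% or more. Every factor in the table except the 1.10 row is less than 10% from 1. The 1.10 row needs insulin-free comparators, and removing it moves 0.825 to 0.75, a fall of 0.075/0.825 = 9.1% from the unadjusted value. So even if insulin were added as a candidate, the stepwise rule could drop it. The sensitivity analysis that adjusts for all identified confounders would not include it either, because insulin is not on the list.

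**The case against.** Much can be said on the other side.

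- A reader might infer that any insulin-treated patient who adds a GTZ is labelled first-line. The protocol does not support that. Only those with no earlier oral drug could reach category 1, and the word "monotherapy", taken literally, keeps even them out. Nor does anything in the protocol rank such patients as the most advanced. This objection stands. The fault is that insulin is left out of the staging, not that advanced patients are assigned to the earliest stage.
- Comparators are not barred from using insulin, so it is wrong to assume that only the exposed arm contains insulin users. This also stands, and it is why the factor carries both shares. It makes the imbalance uncertain but does not create balance.
- The imbalance might be thought beyond adjustment. It is not: duration and HbA1c offset part of it, and insulin prescriptions could be added as a covariate.
- The objective, "comparing individuals treated with glitazones to people treated with agents other than glitazones", might be read as contradicting a comparator rule limited to oral drugs. It does not. The comparator section narrows the broad objective on purpose and says why.
- No analysis by stage category is planned, so no separate category 1 estimate is at risk. That stands. Any effect reaches the primary ratio through the overall insulin shares.
- Code lists and covariate coding often belong in a statistical analysis plan. That is true of the coding. But the stage definition and comparator rule are fixed in this protocol, and once matched sets have been drawn on an oral-only definition, the matching itself cannot be put right without redrawing them.

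**Conclusion.** The point holds in a limited form. Staging and comparator selection count oral drugs only, insulin is neither a matching factor nor a listed covariate, and insulin users who start a GTZ are either without a category or staged as if insulin did not matter. The result is possible residual confounding by disease stage that HbA1c and diabetes duration address only in part.

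Neither size nor direction can be determined from the protocol. On the assumed values tried here, the rate ratio is multiplied by between 0.955 and 1.10, and by 1.00 if the arms have equal insulin shares. The upper end needs 20% insulin use among GTZ users, none among comparators and a 1.5-fold PD rate, so it should not be quoted as an expected bias. The case for changing the plan rests on the gap in a definition whose purpose is to equalise stage, and on the low cost of closing it, rather than on a demonstrated large effect.

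**What to change.** - Add insulin use (yes or no, from prescribing records before or at the index date) to the treatment-stage definition, and state how a GTZ user on insulin is classified.
- Apply the same definition to GTZ users and comparators when matching.
- List insulin use at index as a covariate and keep it in the adjusted model regardless of the 10% change-in-estimate rule.
- Report the insulin share in each arm, so that the factor above can be judged on real values.

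Excluding insulin users from both arms can serve as a sensitivity analysis. Making that the main analysis, or setting up a separately matched insulin category, is a debatable option and is not needed to close the gap.

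The cost is one further code list on prescribing data the study already uses, and a revision of the category and comparator wording before matching. The drawback is that some insulin-treated GTZ users may have fewer than five matches, or none.

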**Exposures, Outcomes and Covariates**

Exposure will be determined by prescribing records, using code lists for individual OADs. Code lists for GTZs can be found in Appendix 1. The index date for each patient will be their first prescribing event that qualifies them for study entry (e.g. first exposure to a GTZ)

The outcome for this study is the first recording of a PD diagnosis after the index date, as identified from clinical and referral records, using the Read code list in Appendix 2. PD due to known causes will be excluded based on the recording of codes presented in Appendix 2.

Covariates to be explored due to their possible association with PD and potential confounding nature will be:

- Smoking status determined using the additional clinical details file
- HRT use determined using prescribing records
- Head trauma as determined by Read code recording
- Age and sex will be accounted for through matching
- Calcium channel blocker use as determined by prescribing records: This exposure has been shown to reduce the incidence of PD (Becker et al, 2008).
- Diabetes itself has been shown to be possibly associated with PD (Wahlqvist et al, 2012). Length of time between diabetes diagnosis and index date, and HbA1c level at index date will be determined and explored for possible confounding properties. In addition, the effect of time updated HbA1c levels will be explored.
- Metformin has been suggested to also have a protective effect against PD (Wahlqvist et al, 2012). As a very commonly prescribed diabetes medication, this will be explored in detail as described below under “Statistical Analysis”.

Other covariates that have not been shown to be associated with PD will also be explored in case of possible confounding, and will include:

- Alcohol consumption
- Body mass index
- Calendar year

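### Treatment-stage category 3 pools a glitazone added to one oral drug with a glitazone added to two or more; with the first-qualifying-event rule for comparators, glitazone users can be at a later diabetes stage even within the category

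*Protocol*

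**What the plan says.** **Stage classification (Protocol, Study Population).** "Users will be classified according to their diabetes treatment stage at the time the GTZ is started", in three categories. The third is "Combined OAD therapy, GTZ being taken with other OADs". It has no count of the other drugs and no time already spent on them. Follow-up of a glitazone user starts at the first glitazone prescription.

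**Comparators (Protocol, Selection of Comparison Group).** The matching rule reads: "Each GTZ exposed patient will be matched by age, sex, and practice with up to 5 patients receiving other oral treatment for diabetes". Stage is not among these listed factors. It is implied by one worked example, for category 1: "For instance a patient could be matched to a GTZ user in category 1) above if they had never received an OAD before 1999". There is no example for category 2 or 3. On entry time: "Follow up for the unexposed will begin at the first prescribing event that makes them eligible for inclusion". On how glitazones were used: "Initially they were mostly used as second line combination treatment, but were subsequently also used at earlier stages of diabetes treatment". The stated reason for restricting comparators to patients on oral treatment is to narrow the difference in disease stage.

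**Covariates (Protocol, Exposures, Outcomes and Covariates).** "Diabetes itself has been shown to be possibly associated with PD". For that reason, "Length of time between diabetes diagnosis and index date, and HbA1c level at index date will be determined and explored for possible confounding properties"; time-updated HbA1c is also to be explored. Number of oral drugs at index is not listed.

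**Model (Protocol, Statistical Analysis).** Confounders stay in the main model only if they change the rate ratio by 10% or more. A separate sensitivity analysis adjusts for all variables identified as potential confounders.

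**The concern.** The design relies on comparing like with like in diabetes stage. Two written rules work against this inside category 3. The category covers a wide span of disease: a patient taking a glitazone as second drug and a patient taking it as third drug after years of dual therapy are classed together. The entry rules then treat the two arms differently within that span. The glitazone user enters when the glitazone happens to start; the comparator enters at the earliest event that qualifies.

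If stage is related to PD, the rate ratio absorbs part of that relation. Should later stage raise PD risk, a protective effect would be diluted or hidden. Should the association run the other way, false protection would appear. Because the asymmetry lies inside the category, making the category a matching factor does not remove it.

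**Working it through.** **1. Entry points under the written rules, category 3**

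| | Glitazone user | Comparator |
|---|---|---|
| Entry event | First glitazone prescription | First event that makes the patient eligible |
| Number of other oral drugs at entry | One, or two or more | Not written; by analogy with the category 1 example, the event that starts combined oral therapy |
| Possible position within the stage | Anywhere | Tends to the start |

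Any imbalance from this source therefore runs towards glitazone users being later.

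**2. The plan's own figure**

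Inputs from Power Calculation: 43,000 exposed, 144 PD events, five comparators each. The significance level is not stated; I assume 5% two-sided. Exposed risk = 144/43,000 = 0.335%; comparator risk = 0.335%/RR. The two-proportion power for RR 0.70, 0.75 and 0.80 is 99.0%, 92.0% and 71.8% (98.9%, 91.3% and 70.3% with continuity correction), against the stated 99%, 91% and 71%. The figures reproduce. They allow nothing for stage imbalance and do not bear on whether it exists.

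**3. Illustrative size of the bias**

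The Protocol gives no third-drug share in either arm and no PD rate by stage, so all inputs here are assumptions. Let s1 and s0 be the shares of the whole glitazone and comparator arms who start a third drug at entry, and k the PD rate at that stage relative to earlier stages. With no adjustment:

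Bias factor = (1 + (k − 1)·s1) / (1 + (k − 1)·s0)

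| s1 / s0 | k = 1.0 | k = 1.1 | k = 1.3 | k = 1.5 |
|---|---|---|---|---|
| 10% / 10% | 1.00 | 1.00 | 1.00 | 1.00 |
| 10% / 0% | 1.00 | 1.01 | 1.03 | 1.05 |
| 25% / 0% | 1.00 | 1.025 | 1.075 | 1.125 |
| 40% / 10% | 1.00 | 1.03 | 1.09 | 1.14 |
| 40% / 0% | 1.00 | 1.04 | 1.12 | 1.20 |

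Example: 40% / 10% at k = 1.3 gives 1.12/1.03 = 1.09. If later stage lowered the PD rate (k = 0.8, shares 25% / 0%), the factor would be 0.95 and a true 0.75 would appear as 0.71.

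**4. What such a factor does to the test**

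Under the null, comparator events = 5 × 144 = 720 and SE(log RR) = √(1/144 + 1/720) = 0.0913. At RR 0.75, comparator events = 720/0.75 = 960 and SE = √(1/144 + 1/960) = 0.0894. Shifting the log rate ratio by log(bias factor), with k = 1.3 and a normal approximation:

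| s1 / s0 | Factor | Two-sided type I error | Power at true RR 0.75 |
|---|---|---|---|
| No imbalance | 1.00 | 5% | 90% |
| 10% / 0% | 1.03 | 6% | 82% |
| 25% / 0% | 1.075 | 12% | 67% |
| 40% / 10% | 1.09 | 15% | 63% |

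**5. Would the 10% rule catch it?**

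A covariate that removed the whole bias would change the estimate by 1 − 1/factor. At 1.09 this is about 8%, so the covariate would be left out of the main model. At 1.12 it is about 11%, so it would be kept. A covariate that captures only part of the bias is kept less readily.

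**The case against.** A reader might infer that comparators always enter at the start of dual therapy and that glitazone users therefore do sit later. The Protocol supports neither as fact.

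- The category 3 comparator event is not written. The text on events that trigger eligibility could be read as the event that makes a patient comparable to a particular glitazone user, which for a third-line user might be a third drug.
- Twelve months of up-to-standard follow-up must precede the comparator's event. A patient already on two oral drugs before then cannot enter at the start of dual therapy.
- No third-line share is given. The text describes mostly second-line combination use at first and earlier use later, and does not mention third-line use.
- Stage matching itself is only implied.

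It would also be wrong to say that diabetes duration and HbA1c are used only if they pass the 10% rule. The fully adjusted sensitivity analysis covers variables identified as potential confounders, and these two may capture much of what drug count would. At the top of the illustrated range, a covariate capturing the whole bias would pass the rule anyway. The direction is open too, since the Protocol calls the link between diabetes and PD only possible.

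All of this stands and limits the point to a risk. It does not remove it. The pooled category and the first-event rule are both written. Drug count is absent from the covariate list on which the sensitivity analysis would draw. The main model, which carries the primary result, can omit duration and HbA1c while a bias below 10% remains. An analysis plan may define the category 3 event, but with the category pooled and first-event entry kept, the natural definition leaves the asymmetry in place.

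**Conclusion.** The point holds as a risk of residual confounding by diabetes stage within category 3. It is not a demonstrated imbalance. Under the assumed shares (10% to 40% of glitazone users, 0% to 10% of comparators) and a later-stage PD rate ratio of 1.0 to 1.5, the rate ratio is multiplied by roughly 1.0 to 1.2; a true 0.75 could appear as anything from 0.75 to 0.90. There is no bias if stage is unrelated to PD or the shares are equal, and the bias reverses if later stage goes with less PD. The type I error of 15% and power of 63% belong to one assumed scenario without adjustment and should not be read as a forecast. The change is worth making because it is cheap and serves the design's own aim of comparable disease stage.

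**What to change.** 1. In Study Population, split category 3 by number of other oral drugs at index: one, and two or more.
2. In Selection of Comparison Group, define the comparator event for each step: a comparator enters at the prescribing event that adds the same-numbered oral drug. State that matching is within that step as well as on age, sex and practice.
3. In Statistical Analysis, always include number of oral drugs at index, diabetes duration and HbA1c at index in the primary model, rather than leaving the last two to the 10% rule.
4. Report glitazone users with no same-step comparator as unmatched. A model term cannot correct for them where there is no overlap.

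The cost is a few sentences in the Protocol and one variable derived from prescribing records already in use. The downside is fewer comparators, and so less precision, for third-line glitazone users.

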**Selection of Comparison Group**

Each GTZ exposed patient will be matched by age, sex, and practice with up to 5 patients receiving other oral treatment for diabetes (unexposed group). To reduce the possibility of confounding, we will only select patients who have also received oral antidiabetic treatments, thus reducing the difference in disease stage between GTZ users and non-users. GTZ prescribing has evolved during >10 years according to changes in treatment guidance and changes made to the licensed indication. Initially they were mostly used as second line combination treatment, but were subsequently also used at earlier stages of diabetes treatment. Rosiglitazone was eventually suspended due to cardiovascular safety concerns and pioglitazone use has waned due to concerns over the risk of bladder cancer. To be considered for inclusion, only patients present in the database from 1999 onwards and with at least 12 months UTS follow up prior to prescribing events that trigger eligibility will be included. For instance a patient could be matched to a GTZ user in category 1) above if they had never received an OAD before 1999 and began taking a sulphonylurea with no other OAD after at least 12 months UTS follow up. Follow up for the unexposed will begin at the first prescribing event that makes them eligible for inclusion.

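### Comparator selection implies matching on treatment stage, but stage and index date are not matching factors and only category 1 has a comparator rule, so time zero may not be comparable

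*Protocol*

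**What the plan says.** Under Study Population, "Users will be classified according to their diabetes treatment stage at the time the GTZ is started". The three categories are glitazone monotherapy with no earlier OAD, glitazone monotherapy after an earlier OAD was stopped, and a glitazone taken together with other OADs.

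Under Selection of Comparison Group, the matching factors are age, sex and practice: "Each GTZ exposed patient will be matched by age, sex, and practice with up to 5 patients". The only stage restriction that covers all comparators is that they have received OADs. One example then suggests selection by category: "For instance a patient could be matched to a GTZ user in category 1) above if they had never received an OAD before 1999" and, continuing, "began taking a sulphonylurea with no other OAD after at least 12 months UTS follow up". Categories 2 and 3 have no such example. On time zero: "Follow up for the unexposed will begin at the first prescribing event that makes them eligible for inclusion". The same section notes that glitazones were at first mainly second-line combination drugs and were later used at earlier stages too.

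Under Exposures, Outcomes and Covariates, time since diabetes diagnosis, HbA1c (at index and time-updated) and calendar year are variables to explore. Treatment stage is not listed. Under Statistical Analysis, a variable stays in the main model only if it changes the rate ratio by at least 10%. Adjustment for all potential confounders is a sensitivity analysis.

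**The concern.** The Protocol relies on its design to make the two groups alike in diabetes stage. That depends on who is matched to whom and when each clock starts, and the text fixes both incompletely.

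There are two separate gaps.

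- **Category 1.** Exposed users must have no OAD history at all. The example holds comparators only to no OAD before 1999. Someone who took and stopped another OAD after 1999 could count as treatment-naive.
- **Categories 2 and 3.** No comparator event is defined, and the comparator enters at its own first qualifying prescription in any year from 1999. A second-line glitazone starter could be set against a patient just beginning first-line treatment, perhaps in a different prescribing era.

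The Protocol itself treats diabetes, its duration and HbA1c as possibly related to PD. A stage gap at time zero could therefore distort the primary rate ratio, and the planned covariate selection need not remove it.

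**Working it through.** **1. The definitions side by side**

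| Element | Glitazone users | Comparators |
|---|---|---|
| Category 1, OAD history | none before the glitazone | none before 1999; no other OAD when the sulphonylurea starts |
| Category 2 | earlier OAD stopped | no rule |
| Category 3 | glitazone with other OADs | no rule |
| Time zero | first glitazone prescription | own first qualifying prescription, not linked to the matched user's date |
| Matching factors | age, sex, practice | age, sex, practice |

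**2. Possible size of a stage imbalance**

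The Protocol gives no stage distribution and no PD rate by stage, so these inputs are assumptions. Let fe and fu be the later-stage shares in exposed and comparators, and R the PD rate ratio for later against earlier stage.

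Bias factor = (1 + fe(R − 1)) / (1 + fu(R − 1))

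With fe = 0.8 and fu = 0.4:

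- R = 1.2: 1.16 / 1.08 = 1.074. A true 0.75 appears as 0.75 × 1.074 = 0.806, hiding 0.056 / 0.25 = 22% of the reduction.
- R = 1.3: 1.24 / 1.12 = 1.107. A true 0.75 appears as 0.830, hiding 0.080 / 0.25 = 32%.

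Other assumed inputs, all with fe = 0.8 and fu from 0.5 to 0.3:

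- R = 1.2: factor 1.05 to 1.09, and 0.75 appears as 0.79 to 0.82.
- R = 1.5: factor 1.12 to 1.22, and 0.75 appears as 0.84 to 0.91.

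If the shares are equal, or R = 1, the factor is 1 and there is no bias.

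**3. Would the 10% rule catch it?**

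Suppose a covariate removed the whole bias. The change as a share of the crude estimate is 1 − 1/1.074 = 6.9% and 1 − 1/1.107 = 9.7%, both under the threshold. As a share of the adjusted estimate it is 7.4% and 10.7%, so only the upper case passes. The Protocol does not say which denominator applies. Duration and HbA1c are proxies for stage, so each may remove only part of the bias and move the estimate less.

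**4. Power, for the cost of a fix**

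Reproducing the stated figures first: take 43,000 exposed, 144 / 43,000 = 0.335% as the exposed risk, that risk divided by the rate ratio as the comparator risk, 5:1, and two-sided alpha 0.05 (assumed; none is stated). A two-proportion calculation gives 99.0%, 92.0% and 71.8% for reductions of 30%, 25% and 20%, against the stated 99%, 91% and 71%. They agree closely.

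A Wald check on the log rate ratio for a 25% reduction uses z = 0.2877 / √(1/144 + 1/(144k/0.75)) and power = Φ(z − 1.96), where k is the number of comparators per user:

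| k | Comparator events | z | Wald power | Two-proportion power |
|---|---|---|---|---|
| 5 | 960 | 3.22 | 0.90 | 0.92 |
| 3 | 576 | 3.09 | 0.87 | 0.89 |
| 2 | 384 | 2.94 | 0.84 | 0.85 |
| 1 | 192 | 2.61 | 0.74 | 0.75 |

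These values keep all 144 exposed events. Any exposed patients left unmatched would lower them further.

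**The case against.** The strongest reply is that the Protocol does not ignore stage. The category 1 illustration speaks of matching to a user in that category and also requires no other OAD when the sulphonylurea starts. A reader might infer from the matching list alone that stage plays no part. The example does not support that. The accurate fault is that stage selection is implied, left off the list and spelt out for one category. Finer rules for categories 2 and 3 could be in an analysis plan that is not at hand, but the matching list, the 1999 test and the time-zero rule are stated here as design features.

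The 1999 gap is also narrower than it looks. A comparator still on the earlier drug fails the example. Because index is the first qualifying event, an earlier OAD start after 1999 would often itself be the index. The gap matters only where that drug was stopped and its start did not qualify, for instance because it fell within the first 12 months of up-to-standard follow-up.

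Three further inferences are tempting but unsupported:

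- That the 1999 gap makes glitazone users the later-stage group. It does the reverse: it admits previously treated comparators opposite first-line users.
- That categories 2 and 3 hold most users. The Protocol says this kind of use predominated initially, and it gives no overall distribution.
- That unequal follow-up length is itself a bias of known size. Poisson regression of rates accounts for person-time, and the document gives no figure for the rest.

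The planned covariates and the fully adjusted sensitivity analysis do reduce the problem. They do not secure the primary estimate, and stage category is not among the listed covariates.

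**Conclusion.** The point holds in this limited form. As written, the matching list, the single category 1 example and the unlinked index dates permit, but do not make certain, a stage or calendar imbalance at time zero that can remain in the primary rate ratio. The two gaps act in different places and can pull in opposite directions, so the net direction is not known.

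If second-line users are set against earlier-stage comparators, with 80% and 40% at later stage and a 20-30% higher PD rate there, the bias factor is 1.07 to 1.11. That would hide roughly a fifth to a third of the 25% reduction that the Protocol calls clinically meaningful, and it could escape the 10% rule. The size rests wholly on these assumed inputs; the structural gap does not. The stated power is not in question. The design should be tightened before data are extracted.

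**What to change.** In Selection of Comparison Group:

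1. Check comparator OAD history up to the index date, not only before 1999.
2. Define the comparator event for each category: first-ever OAD (1); switch to another non-glitazone OAD with the earlier one discontinued (2); addition of a non-glitazone OAD to existing OAD therapy (3). Start comparator follow-up at that event.
3. Add stage category and calendar period of index to the matching factors. Where matching within practice would lose too many sets, force both into the primary Poisson model regardless of the 10% rule.

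This is a text edit before extraction. Full matching would leave fewer comparators per set: power for a 25% reduction would be about 87-89% at 3:1, 84-85% at 2:1 and about 75% at 1:1, against the stated 91%. Some exposed patients, and some of the 144 cases, might find no match. Adjustment instead of matching avoids most of this cost, but it depends on the model to handle any remaining imbalance.
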